## Abstract

**Background:**

Patellofemoral pain (PFP) is highly prevalent in runners, and often leads to functional limitations and cessation of running. Training errors as well as decreased lower limb strength and control during running have all been associated with PFP. While strengthening and gait retraining are commonly used by clinicians, no randomised clinical trial has compared these modalities in runners with PFP. The primary objective of this randomised clinical trial will be to compare the effects of three rehabilitation programs targeting different key factors on symptoms and functional limitations of runners with PFP. The secondary objective will be to explore the factors leading to clinical improvement.

**Methods/design:**

We will conduct a single-blind randomised clinical trial to compare three different 8 week rehabilitation programs: Group 1 will receive education on symptoms management based on training modifications; Group 2 will receive an exercise program targeting lower limb strengthening and control in addition to the education component of Group 1; Group 3 will receive running gait retraining advice as well as the education component of Group 1. Sixty-nine runners with PFP will be recruited and will be seen by independent physiotherapists on five visits through 8 weeks. The primary outcome measure will be symptoms and functional limitations measured by the Knee Outcome Survey – Activities of Daily Living Scale questionnaire at baseline, and at the four, eight and 20 weeks follow-up. Secondary outcomes will include pain level measured using visual analog scales, and running mileage. Lower limb kinematics and kinetics during running, and isometric strength will also be evaluated at baseline and 8 weeks follow-up. The effects of rehabilitation programs on measures of symptoms and functional limitations will be assessed using a 2-way ANOVA (Groups x Time). Regression analyses will be used to identify if changes in running mechanics or strength are determinants of clinical success.

**Discussion:**

Studies with a high level of evidence are needed to determine the best rehabilitation interventions for runners with PFP. This randomised clinical trial will be the first to compare programs targeting different key factors linked with PFP. Results may guide clinicians and improve their clinical outcomes when treating runners with PFP.

**Trial Registration:**

ClinicalTrials.gov: NCT02352909. Registered on December 3, 2014.

## Background

Recreational running has gained popularity among the general population due to its ease of access. Despite all the benefits of recreational running, musculoskeletal injuries are frequent in runners with a reported prevalence of up to 79 %, the knee being the most affected joint. [1] Patellofemoral pain (PFP) has been reported as the most frequent running injury, ranging from 19 to 30 % of diagnostics in women, and 13 to 24 % in men [2, 3]. Thus, it is not surprising that PFP is also known as “Runner’s knee” [4].

Running-related PFP is thought to be caused by a combination of factors that can be related to training errors or to inadequate lower limb muscle strength or control [5–7]. Since running is associated with tremendous cumulative loads in lower limb joints, training errors are believed to be partly responsible for over 60 % of running-related injuries [5, 7, 8]. Clinical observations reveal that runners diagnosed with PFP often had recently incorporated changes in their training regimen such as increases in running mileage or speed, as well as rapid additions of downhill and stairs running [9, 10]. Education on appropriate training loads to respect the envelope of function should therefore be addressed as a main component of interventions in runners with PFP [11, 12].

Several studies have reported that PFP in runners could be related to deficits in lower limb strength. Cross-sectional studies suggest that runners with PFP may present with strength deficits in their knee extensors [13] or hip abductors [14, 15] compared with runners without PFP. However, in two prospective studies involving participants in a start-to-run program, the 21 runners who developed PFP did not have a lower limb strength deficit to these muscle groups prior to their enrolment in the training program [16, 17]. Thus, it can be hypothesised that strength deficits in individuals with PFP may be a result of pain rather than a cause [18].

Lower limb control deficits during running have also been identified in runners with PFP. Noehren et al. found that female runners with PFP exhibited increased peak angles of hip adduction and internal rotation during the stance phase of running compared with healthy female runners [19]. In addition, Willy et al. observed that male runners with PFP had significantly more contralateral pelvic drop than healthy controls, but also showed significantly less hip adduction compared with females with PFP [20]. Based on analyses using dynamic magnetic resonance imaging [21], it could be hypothesised that increased peak hip adduction, hip internal rotation and contralateral pelvic drop during running would result in focal retropatellar overload. Excessive patellofemoral joint forces during running could also potentially be the result of higher ground reaction forces. Specifically, the vertical loading rate of the impact force has been associated with several injuries secondary to a running program [22–24], including PFP [25].

Based on the data presented above, several factors should be considered when selecting a rehabilitation program in runners with PFP. First, the program could simply focus on modifying training loads in order to manage pain and promote tissue adaptation within the envelope of function [11]. Second, exercises targeting the quadriceps as well as hip and core muscles [26] could be prescribed to increase the capacity to sustain loads by strengthening or improving lower limb control. The program could also include gait retraining to decrease forces at the knee during running. Proposed interventions to achieve this goal include increasing step frequency [27], running softer [28] and avoiding a rearfoot strike pattern [29].

To our knowledge, there have been six published studies on rehabilitation interventions in runners with PFP. A recent study from our research group [30] found that an 8 week multimodal program combining education, an exercise program and gait retraining was successful in reducing symptoms and improving function (*n* = 21). Interestingly, reduction in the vertical loading rate was found to be a key factor for improvement. Four other laboratory studies have used gait retraining for runners with PFP. First, Cheung & Davis (*n* = 3) reached clinical success after using feedback for vertical loading rate while runners were asked to avoid a rearfoot strike pattern [31]. This decrease in impact forces was linked with improvements in pain levels and self-reported function. Noehren et al. (*n* = 10) and Willy et al. (*n* = 10; *n* = 2) used a similar training protocol, but provided feedback on peak hip adduction using either a motion analysis system or a mirror [32–34]. In addition to reductions in peak hip adduction angle following gait retraining, participants improved their scores on pain scales. Interestingly, significant reductions in vertical loading rate were also found in Noehren et al’s study [32]. Finally, another study (*n* = 15) reported improvement in symptoms and functional status as well as hip abductor strength following 3 weeks of hip strengthening exercises [15].

While different rehabilitation approaches addressing deficits in runners with PFP show some success in studies with level of evidence of two or three, it is not clear which one is more effective, or why. In fact, no randomised clinical trial has been performed in this population. The primary objective of this randomised clinical trial will be to compare the effects of three rehabilitation programs on symptoms and functional limitations of runners with PFP. The programs will include either education alone, a combination of education and exercises, or a combination of education and gait retraining. The secondary objective will be to identify the factors leading to clinical improvement. Our general hypothesis is that all three interventions will be efficient in decreasing symptoms and improving function. However, based on previously published research in this population, we believe that the group including gait retraining will experience greater and faster improvements than the two other groups. We also hypothesise that changes in running gait pattern associated with a decrease in knee loading and vertical loading rate will be responsible for the greater improvement.

## Methods/design

### Study design

This stratified, single-blind, parallel-group randomised clinical trial will include four evaluation sessions (baseline, week 4, week 8, week 20) and five supervised physiotherapy sessions during an 8 week rehabilitation program. The evaluation sessions will be carried out at the Centre for Interdisciplinary Research in Rehabilitation and Social Integration (CIRRIS) in Quebec City, Canada. The supervised physiotherapy treatments will be conducted at the *Clinique de physiothérapie PCN La Capitale*, a private clinic specialised in the treatment of running injuries. Runners will be allocated to either 1- an intervention that will only include education and training modifications according to symptoms; 2- the addition of a strengthening and lower limb control exercise program to the education component; 3- modifications to the running gait in addition to the education component.

### Participants

Sixty-nine recreational runners with PFP will be recruited through advertisements in running events and sports medicine clinics in Quebec City, Canada, as well as through emails sent to Laval University students and employees. To be included, potential participants will have to meet the following inclusion criteria: 1- age between 18 and 45 years; 2- run at least 15 km per week; 3- present a history of anterior knee pain for at least 3 months; 4- report a pain level of at least 3/10 on a visual analog scale during running and during at least three activities among: kneeling, squatting, stairs and resisted knee extension [35]; and 5- score lower than 85/100 on the Knee Outcome Survey – Activities of Daily Living Scale questionnaire (KOS-ADLS), to ensure a minimum level of symptoms and limitations (clinically important difference of 13.6 points) [36]. In addition, runners will be excluded if they present one of the following conditions: 1- history of lower limb surgery or patellar dislocation; 2- pain believed to originate either from meniscus [37, 38] or from patellar tendon [39]; 3- pain following an acute trauma; 4- concurrent lower limb injuries; 5- history of neurological, inflammatory or rheumatoid disease. A member of the research team will perform a preliminary screening of the inclusion and exclusion criteria and explain the study during a telephone call. If they agree to participate, potential participants will then be met by a physiotherapist to confirm the diagnosis of PFP using the clinical tests. Ethics approval was obtained from the Institutional Review Board of Quebec Rehabilitation Institute (#2014-367), and all subjects will sign a detailed consent form before entering the study.

### Procedures

All included runners will take part in the baseline evaluation session. First, questionnaires on sociodemographic, symptomatology, comorbidity, and running habits will be completed. Thereafter, the level of symptoms and functional limitations will be evaluated using self-reported questionnaires (KOS-ADLS and visual analog scales), before assessing knee and hip muscle strength. Then, lower limb kinematics and kinetics will be evaluated while running on an instrumented treadmill. Finally, runners will be randomly assigned to one of the three intervention groups, and will take part in their assigned 8 week rehabilitation program.

At weeks 4, 8, and 20 (3 months following completion of the program), self-reported questionnaires completed at baseline will be re-administered. This will allow us to determine if a program leads to a faster recovery and to better long-term effects. At week-8 evaluation, lower limb mechanics during running and strength will also be revaluated in the laboratory. All runners will be provided with a GPS-enabled watch (Garmin Forerunner 15) so that running mileage, speed, duration and step count are monitored during the intervention period.

### Randomisation/blinding

A randomisation list will be generated by an independent research assistant (not involved in data collection) using a computer random number generator. Allocation will be concealed in sequentially numbered sealed opaque envelopes. Given the influence of gender and foot strike pattern on lower limb mechanics during running, randomisation will be stratified to ensure balance of the treatment groups with respect to these variables (male/female; rearfoot strikers/non-rearfoot strikers). A block randomisation will also be used to make sure that three equal groups of 23 runners are obtained. Given that it is impossible to blind the treating physiotherapists and the runners, a single-blind design will be used, in which the evaluator will be blinded. Participants will be instructed not to discuss the specific program received with the evaluator.

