
Sample size calculation and statistical analyses: Sample size calculation is based on changes to KOS-ADLS scores, our primary outcome, which are expected to increase following the different interventions. In a previous study using an 8 week multimodal intervention program similar to the current study, KOS-ADLS scores increased from 71.7 ± 12.9 to 89.5 ± 11.9 [30]. Considering similar score changes to our primary outcome, α = 0.05, power of 90 % and CID of 13.6 points for the KOS-ADLS, 20 runners are needed in each group (G*Power 3.1.7). When adding an anticipated attrition rate of 15 %, 23 runners per group are needed; therefore, a total of 69 runners will be recruited. Baseline demographic data will be compared (one-way ANOVA and Chi-squared tests). If baseline characteristics are different across groups, we will adjust group comparisons for confounding variables using an ANCOVA model. An intention-to-treat analysis will be used in which all participants will be analysed in the group to which they were originally assigned, up to the 8 week point. Dropouts or loss to follow-up will not be carried forward to the 3 month follow-up, since a successful outcome after 8 weeks may not necessarily be maintained 3 months later. This will avoid false assumptions regarding durable benefits from the intervention. Per protocol analyses (i.e., analyses restricted to patients who received the intervention as intended) will also be performed. All dropouts and reasons underlying dropouts will be reported. If requested, subjects electing to drop-out will be referred to their treating physician for other treatment options. Any harms or unintended effects during the course of the rehabilitation programs will be reported and discussed. For objective one, a 2-way ANOVA (Groups x Time) will be used to analyse the effects of the rehabilitation programs on KOS-ADLS, VASs and running mileage. For objective two, logistic regression analyses will be performed to identify if changes in running mechanics or strength are determinants of clinical success. For these analyses, results to KOS-ADLS will be dichotomised to changes equal or superior to the CID of 13.6 points, or to changes inferior to this value [36]. Subjective success will also be dichotomised to GRC ≥ +5 or GRC < +5.

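### Sex and foot strike pattern stratify the randomisation but are not named in the primary model, and the stated covariate rule will rarely bring them in: a possible modest loss of precision, not bias

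*Protocol article*

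**What the plan says.** Under Randomisation/blinding, the protocol article gives the reason for stratifying, "Given the influence of gender and foot strike pattern on lower limb mechanics during running", and then the design: "randomisation will be stratified to ensure balance of the treatment groups with respect to these variables (male/female; rearfoot strikers/non-rearfoot strikers". It adds: "A block randomisation will also be used to make sure that three equal groups of 23 runners are obtained".

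The statistical paragraph at the end of the Rehabilitation programs section names the model for the first objective: "a 2-way ANOVA (Groups x Time) will be used to analyse the effects of the rehabilitation programs on KOS-ADLS, VASs and running mileage". The abstract names the same model. Neither place mentions sex or foot strike pattern.

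The same paragraph does have a rule for covariates: "If baseline characteristics are different across groups, we will adjust group comparisons for confounding variables using an ANCOVA model". The comparison that precedes it is of baseline demographic data, by one-way ANOVA and chi-squared tests.

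**The concern.** The factors used to randomise are normally carried into the model. Stratified blocks make the groups more alike on those factors than chance alone would. If the factors predict the outcome, a model without them leaves their variance in the error term and takes no credit for the balance. Standard errors are then too large and the test rejects too seldom under the null.

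The covariate rule does not repair this. It acts on observed imbalance, which stratification is meant to remove for exactly these two variables. Foot strike pattern may not even count as demographic data. So the rule could admit other covariates while passing over the two chosen at the design stage. With about 20 evaluable runners per group, lost precision matters.

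**Working it through.** **Inputs from the article.** KOS-ADLS SD 12.9 before and 11.9 after treatment in the sponsor group's previous study; "α = 0.05, power of 90 % and CID of 13.6 points"; 20 evaluable runners in each of three groups; visits at baseline and weeks 4, 8 and 20. **Assumption.** R², the share of variance explained by sex and foot strike, is not given; it is varied from 0 to 0.30.

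**1. The stated sample size.** For two groups at one time point, two-sided, n = 2(1.960 + 1.282)² × 12.9² / 13.6² = 18.9, so 19 by the normal formula. The exact noncentral t calculation gives 20 (power 0.901), the stated figure. With SD 11.9 the results are 17 and 18. The 20 per group therefore reproduces without any strata adjustment.

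**2. Single-time group contrast.** Unadjusted SE = 12.9 × √(2/20) = 4.08. With the strata in the model, SE = 4.08 × √(1 − R²). The unadjusted SE is too large by the factor 1/√(1 − R²). Approximate power is Φ(13.6/SE − 1.96).

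| R² | SE with strata | Unadjusted SE too large by | Power with strata |
|---|---|---|---|
| 0 | 4.08 | 0% | 0.915 |
| 0.05 | 3.98 | 2.6% | 0.928 |
| 0.10 | 3.87 | 5.4% | 0.940 |
| 0.15 | 3.76 | 8.5% | 0.951 |
| 0.20 | 3.65 | 11.8% | 0.961 |
| 0.30 | 3.41 | 19.5% | 0.979 |

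**3. The planned four-visit model.** The table does not carry over directly, so the design was simulated: 60 runners, three groups, four visits, and stratified blocks of three (the article gives no block size). Between-runner and residual variance were equal. Half the runners were of each sex, a quarter were non-rearfoot strikers, and the strata effect acted through sex. There were 3000 runs per scenario, so the Monte Carlo standard error of a 5% rejection rate is √(0.05 × 0.95/3000) = 0.004. R² is the share at one visit (the last visit in the second case below).

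- *Strata effect constant over time.* The mean SE for change from baseline to the last visit is 0.314 to 0.316 with or without the strata, at every R². Type I error for that contrast and for Group x Time is 0.042 to 0.053, with no trend. The effect cancels within each runner. The Group main effect is conservative: at R² = 0.10 the mean model SE is 0.272 against an empirical SD of 0.253 (type I error 0.038); at 0.30 it is 0.325 against 0.249 (0.009). The inflation exceeds step 2 at the same R² because averaging four visits reduces noise. At R² = 0.10 the strata variance is 0.10/0.90 = 0.111 and the rest is 0.5 + 0.5/4 = 0.625, so the share in the mean is 0.111/0.736 = 0.15, which step 2 converts to 8.5%.
- *Strata effect growing over the visits.* The change contrast is now conservative too: SE 0.333 against 0.308 at R² = 0.10 (type I error 0.032), and 0.378 against 0.324 at 0.30 (0.022). Group x Time type I error falls to 0.025 at R² = 0.30. Putting the strata in the model for change, which corresponds to strata-by-time terms in the repeated-measures model, brings the SE to 0.315 or 0.316 and type I error to 0.043 to 0.054.
- *R² = 0.* Omitting the strata makes no difference.

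**4. Degrees of freedom, KOS-ADLS.** Between runners: 60 − 3 = 57, of which two binary factors use 2. Within runners: 57 × 3 = 171, of which two factors by three time contrasts use 6.

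**The case against.** The strongest reply is that the trial's hypothesis, that gait retraining gives larger and quicker gains, is carried by the Group x Time term, and a stable effect of sex or foot strike cancels from it. This stands, and the simulation confirms it. A reader might infer that the primary test's standard errors are overstated by the percentages in the table. The documents do not support that: the percentages apply to between-runner comparisons, and the interaction is affected only if the factors change the course of recovery. Such an effect is plausible on the article's own reasoning. It links both factors to running mechanics, expects mechanical change to drive improvement, and has some gait-retraining runners alter their foot strike. It is not demonstrated.

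Second, the factors are said to influence mechanics. Nothing says that they predict KOS-ADLS, a questionnaire on symptoms and daily activities. This stands too, so the loss is conditional.

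Third, a condensed article may leave covariates to a fuller plan that is not shown, and it nowhere says that the strata will be excluded. This holds in part. Had the article been silent on covariates, there would be no point to make. But it states a rule for when covariates enter, and that rule works against the stratification factors. Equally, it would be wrong to read the plan as allowing no adjustment at all, since the conditional ANCOVA exists.

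**Conclusion.** The mismatch between design and analysis is real, and its consequence is modest. If sex and foot strike explain 5% to 15% of the variance in the quantity compared (an assumption), omitting them makes the standard errors of between-runner contrasts about 2.6% to 8.5% too large. For the Group x Time test the cost is nil if their effect is stable over time, and appears only if they alter recovery. If they explain nothing, nothing is lost.

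A reader might go further and conclude that the treatment comparison is biased, prone to false positives or underpowered. None of these follows. Any error is conservative, and the planned 20 per group reaches 90% power without the strata on the calculation that reproduces it.

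**What to change.** State in the analysis section that sex and baseline foot strike pattern (rearfoot or non-rearfoot), each with its interaction with time, are in the KOS-ADLS, VAS and mileage models, independent of any baseline comparison. Main effects alone are not enough: they sharpen the Group main effect but leave the Group x Time test essentially unchanged. Foot strike must be the value used for stratification, since gait retraining can change it later.

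The cost is one sentence and, for KOS-ADLS with 60 completers, the 2 of 57 and 6 of 171 degrees of freedom shown above. No new data are needed, because both factors must be known before a runner can be randomised. For these two variables, it also removes a covariate choice that depends on the data.
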